### Interim analyses {21b}

No interim analysis will be performed and no early stopping rule for futility is proposed.

### Methods for additional analyses (e.g. subgroup analyses) {20b}

An economic evaluation taking the form of a cost-effectiveness analysis (CEA) will be conducted to compare the efficiency of spironolactone and cycline treatment. The analysis will be conducted from the societal perspective, which means that costs to hospitals, the National Health Insurance System and patients will be considered, over a 6-month time horizon, to be consistent with the primary endpoint. The main judgement criterion will be the incremental cost-effectiveness ratio defined as a cost per QALY gained. To estimate QALYs, patients will be asked to fill in the EuroQol EQ-5D health-related quality of life questionnaire.

For the estimation of costs, resources consumed will be recorded prospectively in the patient’s diary for a period of 6 months following the start of the treatment. The main resources to be collected are in the patient diary are: * Medication * Ambulatory physician visits * Dermocosmetic care.

Unit costs will be estimated using conventional tariffs from the French National Health Insurance System to value ambulatory care consumption. Costs in each arm will be estimated by multiplying the amount of each type of resource consumed by their corresponding unit monetary value. In CEA, the outcomes of an intervention are evaluated in terms of the QALY, which is a numerical composite measure that encompasses information about the length of life and the health-related quality of life. They are computed by weighting each year by a corresponding quality of life factor, usually ranging from 0 (death) to 1 (perfect health). Quality of life weights will be obtained by asking patients to answer the EuroQol EQ-5D quality of life questionnaire at baseline and at 2, 4, and 6 months from baseline. The difference in QALYs between the two arms of the study will be calculated using analysis of area under the curve, with linear interpolation of utility scores between measurement time points.

The EQ-5D will also be applied at 9 and 12 months to evaluate quality of life up to M12, as a secondary objective, independently from the cost-effective analysis. The ICER (see below) comparing the spironolactone and cycline arms will be analysed using a non-parametric bootstrap approach to produce estimated confidence intervals at 95% over the mean ICER:
$$ \mathrm{ICER}=\left[{\mathrm{Costs}}_{\mathrm{Spironolactone}}-{\mathrm{Costs}}_{\mathrm{Cycline}}\right]/\left[{\mathrm{QALYs}}_{\mathrm{Spironolactone}}-{\mathrm{QALYs}}_{\mathrm{Cycline}}\right] $$

The cost-effectiveness of spironolactone will be assessed according to a willingness to pay of 50,000 euros. The probability of cost-effectiveness will also be assessed with several willingness to pay thresholds and will be represented in an acceptability curve. A sensitivity analysis will be performed in order to assess the robustness of the ICER result.

### Methods in analysis to handle protocol non-adherence and any statistical methods to handle missing data {20c}

All participants will receive the assigned study treatment until unacceptable toxicity, death, loss to follow up, withdrawal of consent or termination of the study by the Sponsor, in accordance with local standards of care. Unacceptable toxicity and death will be considered as failure for the primary criteria analysis. Loss to follow up, missing data for the primary criteria and early termination of the study by the Sponsor will be also considered as failures by the ITTm and not replaced.

Patients who did not fulfil the inclusion criteria after randomization and those who never began their treatment will be replaced. For the clinical secondary criteria analysis, patients with missing data will be withdrawn. Missing data in cost-effectiveness analysis will be handled according to a multiple imputation method in the ITTm sample. If a patient is released from the study (e.g. in the event of adverse reactions (ARs) preventing the continuation of the study), her data will not be collected, except for safety data (follow up of ARs or onset of ARs associated with the experimental treatment, based on pharmacokinetic data).

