### Sample size {14}

For sample size estimation purposes, the targeted difference in the percentage of success is 70% in the experimental arm compared with 50% success in the control arm, indicating a relative increase in success equal to 40%. Assuming a type I error rate of 5% and at least 80% statistical power, the sample size required is at least 91 subjects per group. To take into account the possibility of patients being lost to follow up, 10% (9 subjects) will be added to each group. Finally, approximately 200 subjects will be randomized to the two arms in a 1:1 ratio.

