### Recruitment {15}

Acne vulgaris is a common condition. However, it is more common in the private sector than in public hospitals. Some centres such as Nantes have a one-day consultation devoted to acne. A feasibility study performed in each centre showed that between 8 and 15 patients per centre could be included per year, making these recruitment targets achievable.

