### Statistical methods

#### Statistical methods for primary and secondary outcomes {20a}

The primary efficacy variable is the percentage of success defined in “Background and rationale” (paragraph 2.1.2). The comparison between the two arms will be done using a Cochran–Mantel–Haenszel test checking for class of contraception (four strata). Modified intention to treat (ITTm) andlysis will be applied. That implies that to maintain the initial statistical power of the ITTm analysis, all randomized patients will be included in the final analysis, minus those who did not fulfil the inclusion criteria after randomization and those who never began their treatment.

All secondary objectives are expressed as a percentage or a status at a fixed time of follow up. General linear mixed models will be planned to take into account the repeated measurements collected on the same participant during their follow up. The Cox model with time-dependent covariates can also be used for secondary objectives for which a status is considered. Significance will be set at 5% in a bilateral situation.

For the cost-effectiveness analysis, 95% confidence intervals for differential (between arms) costs and QALYs and for the incremental cost-effectiveness ratio (ICER) will be estimated using the non-parametric bootstrap estimation procedure.

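### Women cut short because the Sponsor ends the study for an administrative reason would be counted as treatment failures, which dilutes the treatment difference

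*Protocol article*

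**What the plan says.** The section on non-adherence and missing data {20c} names several reasons why assigned treatment may end, among them "withdrawal of consent or termination of the study by the Sponsor". It first scores unacceptable toxicity and death as failures for the primary criterion. It then adds: "Loss to follow up, missing data for the primary criteria and early termination of the study by the Sponsor will be also considered as failures". It makes no exception for a stop that has nothing to do with the drugs.

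The statistical methods section {20a} removes only two groups from the modified intention-to-treat set: women found not to meet the inclusion criteria and women who never began treatment. Women cut short by the Sponsor therefore remain in the denominator. The primary endpoint is the best response over the M4 and M6 assessments (comparator section {6b}; Outcomes {12}).

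On stopping, section {21b} says: "No interim analysis will be performed and no early stopping rule for futility is proposed". The sample size section {14} sets its 10% allowance against loss to follow-up only.

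**The concern.** Toxicity, death and drop-out can each reflect the treatment, so scoring them as failure is a defensible composite and is not contested here. An administrative stop is different. It is a calendar event that catches women by date of randomisation, about equally in two arms allocated 1:1. A woman halted at M2 because funding ended has not failed treatment; she was not observed.

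The clause operates only if the study is terminated. In that case it would lower both reported success rates, shrink their difference, and take power from a trial already short of information. The text also leaves open what happens to a woman with a recorded success at M4 whose M6 visit is cancelled by the stop. Read literally, the clause could turn her success into a failure.

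**Working it through.** **Inputs from the article.** "the targeted difference in the percentage of success is 70% in the experimental arm compared with 50% success in the control arm" (Sample size {14}); "Assuming a type I error rate of 5% and at least 80% statistical power" (same section); "Significance will be set at 5% in a bilateral situation" (Statistical methods {20a}); about 200 women allocated 1:1, so 100 per arm; recruitment over 41 months (Participant timeline {13}).

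**Assumptions, not in the article.** Uniform accrual; follow-up halted on the day of the stop; truncation equal in the two arms and unrelated to outcome. The article gives no value for the share f cut short.

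**Step 1: the plan's own figure.** The article states "the sample size required is at least 91 subjects per group". The unpooled two-proportion formula gives (0.70×0.30 + 0.50×0.50) × (1.960 + 0.8416)² / 0.20² = 0.46 × 7.849 / 0.04 = 90.3, rounded up to 91. The figure reproduces, and adding 9 gives 100 per arm.

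**Step 2: effect of the rule.** Scoring a share f as failures changes the rates to 0.70(1−f) and 0.50(1−f).
- The difference becomes 20(1−f) points.
- The odds ratio moves toward 1, from 2.33 at f = 0 to 2.08 at f = 10%.
- The ratio of success rates stays at 0.70/0.50 = 1.40.
- If the true rates are equal, the diluted rates are equal too, so type I error is not inflated.

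**Step 3: plausible f at full accrual.** 200/41 = 4.88 women per month. On the last recruitment day, 4 × 4.88 = 19.5 women (4/41 = 9.8%) are short of M4 and 6 × 4.88 = 29.3 (6/41 = 14.6%) are short of M6.

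**Step 4: power.** A normal approximation without strata is used: power = Φ[(d − 1.96·se₀)/se₁], where se₀ uses the pooled rate and se₁ the separate rates. *Scored as failures* keeps 100 per arm with diluted rates; *left out* uses 100(1−f) per arm at 70% and 50%.

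Worked at f = 10%:
- Scored as failures: d = 0.18, se₀ = √(0.54×0.46×2/100) = 0.0705, se₁ = √[(0.63×0.37 + 0.45×0.55)/100] = 0.0693, so Φ(0.604) = 72.7%.
- Left out: 90 per arm, d = 0.20, se₀ = 0.0730, se₁ = 0.0715, so Φ(0.795) = 78.7%.

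| f | Diluted rates | Difference | Power, scored as failures | Power, left out |
|---|---|---|---|---|
| 0 | 70% v 50% | 20 points | 82.8% | 82.8% |
| 4/41 = 9.8% | 63.2% v 45.1% | 18.0 points | 73.0% | 78.8% |
| 6/41 = 14.6% | 59.8% v 42.7% | 17.1 points | 67.8% | 76.5% |

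The last row applies if the clause also overrides a recorded M4 result. If women seen at M4 are classified on M4, only the 9.8% are unobserved. The exact power then depends on the success rate at M4 alone, which the article does not give.

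**Step 5: an earlier stop.** At month 24, 24 × 4.88 = 117 women are randomised, about 59 per arm. The share short of M4 is 4/24 = 16.7%. Power is 44% scored as failures and 53% left out. Even with all 59 per arm assessed it would be only about 60%.

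**The case against.** Several points on the other side are sound and limit the concern.

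- **The event is not planned.** No scheduled efficacy look leads to termination, and the article gives no probability for it. Without termination the effect is zero. Stopping recruitment while completing follow-up also gives f = 0.
- **Accrual does not make it likely.** A reader might infer otherwise from the Recruitment section, which expects "between 8 and 15 patients per centre could be included per year". At the low end, the seven centres under Study setting {9} give 7 × 8 × 41/12 = 191 women. But the high end is 7 × 15 × 41/12 = 359, 191 exceeds the 2 × 91 = 182 required, and power with 191 is about 81%. The article does not support calling termination a realistic prospect.
- **Large f does not go with 100 per arm.** A reader might apply 20% or 25% truncation to the full sample. Under uniform accrual over 41 months that cannot arise. It needs a much earlier stop, when power is low under either rule.
- **A Sponsor stop may concern the drugs.** The data monitoring section {21a} has a safety committee advising the Sponsor, including on risk/benefit questions. It would be wrong to treat every Sponsor termination as uninformative.
- **The rule is conservative.** With equal truncation it cannot favour spironolactone in a superiority test. Scoring all missing outcomes as non-response is a recognised convention, and leaving out treated women departs further from intention to treat.

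What survives is narrower. For an administrative stop, the stated rule records an outcome that was never observed and loses more power than the missing information requires. The analysis plan is not shown, so the absence of a sensitivity analysis in the article is not a criticism.

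**Conclusion.** The point holds as a cheap improvement to a contingency clause. The article fixes the rule explicitly and nothing elsewhere in it reverses it. If the Sponsor stops for an administrative reason before some women reach M4 or M6, both success rates and their difference are understated by the factor (1−f). For an abrupt stop at full accrual, the avoidable loss of power is about 6 points at f of about 10% and about 9 points at f of about 15%. These sizes rest on the planned 70% and 50%, uniform accrual, equal truncation in the two arms and follow-up halted at once.

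A reader might infer that the clause threatens the trial's validity or could produce a false claim of superiority. It does neither: the bias is toward no difference and arises only on termination.

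**What to change.** In section {20c}, take administrative termination by the Sponsor out of the list of failures, and state that:

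1. a woman with an M4 assessment whose M6 visit was prevented by the stop is classified on M4;
2. a woman with neither M4 nor M6 solely because of an administrative stop, identified by date alone, is administratively unobserved and left out of the primary analysis;
3. the version scoring all such women as failures is reported as a sensitivity analysis;
4. the exception does not apply when the stop was prompted by safety or efficacy findings.

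Keep the failure rule for toxicity, death, loss to follow-up and other missing primary data. Identification by date leaves no room for selective exclusion. Multiple imputation of these women would be an acceptable alternative to leaving them out.

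The cost is one clause now and, only if the trial is terminated, a slightly smaller analysis set and one extra table. The change should be made before any termination is in view, since a later change would look driven by the data.

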## Interventions

### Explanation for the choice of comparators {6b}

As already stated, although acne is not an infectious disease, oral antibiotics have remained a mainstay of treatment over the last 40 years. The anti-inflammatory properties of oral antibiotics, particularly cyclines, are effective in treating inflammatory acne [39, 40].

All the guidelines - French [41], European [42] and American [43] - recommend cycline for first-line treatment but limited to a treatment period of 3 months to minimize the development of bacterial resistance. This is why the treatment duration of the comparator arm we chose is doxycycline 100 mg/day for 3 months. The guidelines specify also that monotherapy with a systemic antibiotic is not recommended. Concomitant topical therapy with, for example, benzoyl peroxide should be used with systemic antibiotics and for maintenance after completion of systemic antibiotic therapy. Patients in the two study arms will receive this topical therapy.

The primary objective is the efficacy of doxycycline or spironolactone seen at M4 and/or M6. To avoid results bias and because our experience shows that maximum efficacy is seen for cycline between M4 and M6, the best clinical response between M4 and M6 will be chosen for the primary endpoint.

The response of acne to spironolactone may not be optimal after only 3 months of treatment [22]. A retrospective trial reported by Burcke and Cunliffe showed an average reduction in acne that was optimal at month 6 [24].

In conclusion, in order not to bias the study in either direction, regarding the primary objective, the efficacy of the two treatments will be measured at 4 and 6 months in each arm and the best results in the two arms will be compared (Fig. 1). At the end of the M6 visit, after the clinical evaluation, all the data will be accessible and open to the patient and the investigator. Patients with complete or partial remission will continue the trial. Other patients will drop out of the trial and be treated by the investigators according to their usual practice. The same approach will be used at the M9 visit: relapse patients will drop out of the trial and will be treated by the investigators according to their usual practice.

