### Outcomes {12}

The primary endpoint corresponding to the treatment efficacy is determined by the probability of success in each arm. In order to reduce the variability related to the fluctuation over time of the therapeutic response, we took the maximum value of this response. This maximum value appears between the fourth and sixth month of treatment. We could also have taken the average measured over 2 months, but clinically this is not interesting because the optimal time of efficacy is different between the two treatments This probability of success (or relapse) is defined by a decrease in both AFAST scores: (1) AFAST score 1 (corresponding to the GEA score): decrease of at least two grades compared to baseline or to grade 0 if the baseline was at 1, and (2) AFAST score 2 (mandibular score): decrease to grade 1 if baseline was > 1 or to grade 0 if the baseline was at 1.

AFAST score 1 (also called GEA) assesses the comedones (open and closed), the non-inflammatory lesions, the papules and pustules and the nodules. The stage is defined according to a global evaluation of severity of acne and ranges from grade 0 (no acne) to grade 5 (the worst situation). AFAST score 2 assesses acne on an area from the left and right mandibular zone to the upper edge of the trunk and ranges from grade 0 (no acne) to grade 3 (the worst situation).

For the secondary endpoints:
Safety/tolerance: reporting of the number and type of adverse events (AEs) and serious adverse events (SAEs) up to month 12 of follow up and abnormal values of ionogram (sodium, potassium, chlorine and calcium) at 0, 2, 4 and 9 months. First the percentage of AEs and SAEs will be calculated then they will be classified according to the organ affected.Efficacy: these outcomes correspond to the reporting of the:
Number of patients with AFAST score 1 (GEA) at 0 or 1, at M2, M4, M6, M9 and M12Number of patients with AFAST score 2 (mandibular) at 0 or 1, at M2, M4, M6, M9 and M12Number of patients with both AFAST scores 1 and 2 at 0 or 1, at M2, M4, M6, M9 and M12Number of inflammatory lesions of the face at D0 (baseline), M2, M4, M6, M9 and M12Number of retentional lesions of the face at D0, M2, M4, M6, M9 and M12Number of face lesions at D0, M2, M4, M6, M9 and M12Number of trunk lesions (factor F2 of ECLA) at D0, M2, M4, M6, M9 and M12Number of patients with relapses at M4 and M6

The definition of relapse is the same as the primary endpoint:

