## Assignment of interventions in a double-blind method

### Who will be blinded {17a}

Our study is a randomized double-blind trial during the first 6 months (timeline for the primary objective), and an open tria during the last 6 months of follow up. The female patients will be randomized either to the acne routine care arm, i.e. cycline (doxycycline 100 mg/day for 3 months followed by a placebo for 3 months) or to the experimental drug arm (spironolactone 150 mg/day for 12 months).

The patients and the investigators and their teams will only be blinded to the treatment assigned during the first 6 months. As Karanicolas et al. pointed out in their article from 2010, their study should have been masked to the biostatisticians until analyses had been performed, to reduce the study bias [45].

Blinding will be removed for all patients after 6 months of evaluation - once the primary endpoint has been measured - whatever the result, to limit the constraints for the patients in the doxycycline arm. If blinding were maintained, patients in the doxycycline arm would have to take a placebo for up to 6 months in addition to the 3 months already taken. The objective of the last 6 months of follow up is to assess the maintenance of the efficacy of each treatment during this time.

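### Between-arm results at M9 and M12 come only from women kept in the trial because they responded, so they are not randomised comparisons

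*Protocol article*

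**What the plan says.** All references are to the protocol article.

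- **Selection at M6.** Under Explanation for the choice of comparators {6b}, women in complete or partial remission go on. "Other patients will drop out of the trial and be treated by the investigators according to their usual practice". Intervention description {11a} likewise withdraws women who fail to respond from M6 onwards.
- **Selection at M9.** The same {6b} section says that "relapse patients will drop out of the trial" at that visit.
- **Data after release.** The section on non-adherence and missing data {20c} ends collection for a woman released from the study, apart from safety data.
- **Exclusion rule.** {20c} adds: "For the clinical secondary criteria analysis, patients with missing data will be withdrawn". Counting missing results as failure is stated there for the primary criterion only, and multiple imputation for the cost-effectiveness analysis only.
- **Comparisons still planned.** Objectives {7} and Outcomes {12} list AFAST scores of 0 or 1, complete remission, lesion counts and quality of life at M9 and M12, for comparison between the arms.
- **Purpose of months 6 to 12.** Who will be blinded {17a} gives it as "to assess the maintenance of the efficacy of each treatment during this time".
- **Model.** Statistical methods {20a} plans mixed models for the repeated measurements on each participant.

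**The concern.** Whether a woman contributes efficacy data at M9 depends on how she responded by M6. Whether she contributes at M12 depends also on whether she had relapsed at M9. Both are outcomes of treatment. If the drugs differ in response, as the trial hopes to show, the women left in the two arms are different fractions of those randomised, and probably differ in prognosis. Comparing them no longer has the protection of randomisation.

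The exclusion rule in {20c} makes this a stated analysis choice and not a detail left open: nothing puts the withdrawn women back into the denominator. Every between-arm efficacy and quality-of-life result at M9 and M12 is affected. A contrast of continuing women could be published as a 12-month treatment comparison when it answers a different question.

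**Working it through.** **1. The plan's own figure.** Sample size {14} assumes success in 70% v 50%, "Assuming a type I error rate of 5% and at least 80% statistical power". Statistical methods {20a} adds: "Significance will be set at 5% in a bilateral situation". With the unpooled normal approximation:

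n = (0.70 × 0.30 + 0.50 × 0.50) × (1.960 + 0.842)² / 0.20² = 0.46 × 7.85 / 0.04 = 90.3, so 91 per group.

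This matches the stated 91, and the 9 added per group give 100. The figure concerns the primary endpoint and is not in question. I use 100 women per arm below.

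**2. Who is left at each visit.** At M9: women kept at M6. At M12: women kept at M6 who had not relapsed at M9. The protocol gives no figure for either fraction.

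**3. Illustration with M6 withdrawals only.** Let r be the share retained at M6 and m the share of those still in response later. Continuing women show m. The full modified intention-to-treat (ITTm) denominator, with withdrawn women counted as non-responders, shows r × m. Both r and m are assumed; m is 80% in each arm.

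| Retained at M6 | Continuing women | Full ITTm denominator | Difference, full denominator |
|---|---|---|---|
| 70% v 50% | 80% v 80% | 0.70 × 0.80 = 56% v 0.50 × 0.80 = 40% | 16 points |
| 90% v 85% | 80% v 80% | 0.90 × 0.80 = 72% v 0.85 × 0.80 = 68% | 4 points |

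For a common m from 60% to 90%, the first row gives 20 × 0.60 = 12 to 20 × 0.90 = 18 points, and the second 5 × 0.60 = 3 to 5 × 0.90 = 4.5 points.

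**4. Adding the M9 withdrawals.** Assume 70 v 50 women retained, relapse by M9 in 10% v 40%, then relapse in 10% of each arm by M12.

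- Women left after M9: 70 × 0.90 = 63 v 50 × 0.60 = 30. Their M12 result is 90% v 90%.
- Full denominator: 0.70 × 0.90 × 0.90 = 56.7% v 0.50 × 0.60 × 0.90 = 27.0%.
- Among all women who continued at M6: 0.90 × 0.90 = 81% v 0.60 × 0.90 = 54%.

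Here maintenance does differ between arms, and the M12 analysis of women with data does not show it.

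**5. A difference without a drug effect on maintenance.** In a simulation, response and maintenance shared a latent prognosis, the drug had no effect on maintenance, overall maintenance was 60%, and 70% v 50% were retained. The responders-only contrast was -2.3, -5.8 and -8.3 points (against spironolactone) for latent coefficients of 0.5, 1.0 and 1.5. These coefficients are assumptions; the result shows direction and possibility, not expected size.

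**6. The two sections side by side.** The mixed models in {20a} can use women with some visits missing. The rule in {20c} excludes patients with missing data. If it applies per visit, it affects M9 and M12 alone as far as these withdrawals are concerned. If it applies to the whole patient, women withdrawn at M6 also vanish from the M2 to M6 secondary analyses. The wording allows both.

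**The case against.** The strongest reply is that the last six months are meant to show how well each treatment holds its effect, a within-arm question for which responders are the natural cohort. In step 3 maintenance is set equal, so 80% v 80% is the right answer about maintenance, and the 16 points are merely the assumed M6 gap carried forward (20 × 0.80). Both points stand. A reader might infer that the M9 and M12 data say nothing about maintenance; that goes too far. What fails is reading the between-arm contrast as randomised, and Objectives {7} plans that contrast. Step 4 adds that even a within-arm M12 figure needs all women who continued at M6 as its denominator.

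Other stronger readings are also unsupported:

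- **70% v 50% as M6 retention.** Those are assumed success rates on the primary endpoint, the best response at M4 or M6. Continuation rests on complete or partial remission, and partial remission is not defined against the primary rule. Retention could be higher and closer between arms, hence the second row in step 3.
- **All M6 failures lost from M2 to M6.** This is one reading only. Outcomes {12} calculates percentages at each time point, which fits exclusion per visit at least as well.
- **Maintenance left unmeasured because relapse is an endpoint only at M4 and M6.** AFAST scores and lesion counts are outcomes at M9 and M12, and relapse is judged at M9 because it triggers withdrawal.
- **A fixed inflation of adverse events in the arm with more responders.** Outcomes {12} says: "First the percentage of AEs and SAEs will be calculated then they will be classified according to the organ affected". These are percentages, some safety collection continues after release under {20c}, and retention is unknown, so no figure can be given. At most, adverse-event follow-up after M6 may differ by arm.

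**Conclusion.** The point holds for the between-arm comparisons at M9 and M12. By the protocol's own rules they are made among women selected after randomisation on response, and they cannot be presented as randomised comparisons. Results in responders remain usable as a description within each arm. The exclusion rule in {20c} and the models in {20a} need to be reconciled whichever reading was meant.

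The size is unknown. The illustrations (16 points at 70% v 50% retained, 4 points at 90% v 85%, both with an assumed common 80% maintenance) measure how far the two denominators differ, not a bias to be expected. If retention and prognosis turn out alike in the two arms, the M9 contrast would be little affected; the M12 contrast could still be distorted by the M9 withdrawals.

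The primary endpoint, its rule of counting missing results as failure, the sample size and the six-month economic analysis are unaffected. The fault lies in secondary results from an open-label phase, but it touches every efficacy result at M9 and M12.

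**What to change.** - **Binary secondary endpoints at M9 and M12:** keep the full ITTm denominator. Count women withdrawn for non-response at M6 or for relapse at M9 as non-responders at later visits.
- **Counts and scores:** replace the exclusion rule in {20c} with the mixed models of {20a} fitted to all available visits, so that women withdrawn at M6 or M9 keep their earlier data. These models rest on a missing-at-random assumption, which should be stated.
- **Results in continuing women:** report them by arm, labelled descriptive and non-randomised, with the number who continued at M6 shown.
- **Adverse events:** note that follow-up after M6 may differ by arm, and report M6 to M12 events with person-time.

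The cost is analysis wording. No visit, treatment or data item changes, and the article reports that inclusion was still open. The M9 and M12 percentages will look lower, and they will then describe success of the allocated treatment strategy and not durability among responders, so both should be shown and clearly named.
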